#### Recruitment

Eligible occupational therapy students will be provided with information about the study and invited to participate at the beginning of, or just prior to, the start of the semester in which the trial is to be implemented. All students will be informed that (1) if enrolled in the unit they will undertake either the SCP or TCP as determined by random selection; (2) all students will complete the same instruments towards their assessment and provide feedback on their placement experience; and (3) only data from students who consent to participate will be included in the trial. Students will be told that taking part in the trial and allowing their data to be used is voluntary and that their experience and grades in the unit of study will not be affected should they choose not to participate. Prior experience suggests the recruitment rate of students (with efficient and focussed strategies) will achieve 85–90% of the student population. With multicentre trials, the rate is often less, perhaps 70%, although Watson et al. [22] found that, of 1200 eligible students for a study using simulation to replace clinical time, only 410 students volunteered to participate (34%). Therefore we estimate that a recruitment rate of 60% of eligible students will be achievable. In 2015, the participating universities estimated that 774 students would be eligible for inclusion in the trial in 2016, thus a sample of 425 (55% of the expected eligible sample) appears feasible.

### Randomisation and allocation

Using a procedure specified by the national research team, the local research assistant at each site will recruit students to the trial, collect consent forms and allocate students to either the SCP or TCP group in a 1:1 ratio. A software package will be used to generate the random allocation sequence of students who have consented to submit their data for the trial. This software is freely available from the Internet (http://random-allocation-software.software.informer.com/2.0/) and is described in the literature [34]. The allocation is performed at each site by the local research assistant utilising block randomisation once student enrolment in the unit of study is determined.

### The SCP intervention

The SCP, called *OTSimPrac*, aims to fully substitute 40 hours (a 5-day working week) of TCP. It is designed to be situated in the foundation years of an occupational therapy program where the focus of learning is on development of professional behaviours, self-management, communication and information-gathering skills that are applicable in all placement or work settings. The SCP is designed to address criteria stipulated by the Occupational Therapy Council for simulation-based placement with the aim of being eligible to contribute to the 1000 hours of clinical placement mandated within the Occupational Therapy Accreditation Standards [11]. Examples of how these five criteria are addressed are provided in Table 1.

**Table 1 Tab1:** Design features of the SCP in relation to the five criteria set by Rodger et al. (2010) [21]

Design criteria	Operationalised in the SCP by:
1. High level of authenticity for occupational therapy (OT) practice	• Development of authentic case studies and validation of case studies by external healthcare professionals • Setting the pace and duration of the SCP to reflect a realistic timeframe for the actual clinical processes • Conducting simulated clinical activities in authentic environments (simulated or actual practice environments) • Providing opportunity for the students to learn through observation/role modelling and by working alongside each other • Including and assessing a breadth of skills, knowledge and attributes rather than isolated or de-contextualised components • Requiring individual- and group-based activity engagement by each student • Requiring students to interview and communicate with clients, healthcare professionals and other stakeholders (e.g. employers of clients in a vocational rehabilitation setting) within the client intervention process • Using authentic clinical/professional tools and processes in developing rehabilitation/intervention plans • Requiring students to communicate assessment results and intervention recommendations with clients and key stakeholders via clinical conferences, presentations and written reports and/or other professional documentation • Providing students with feedback from clinical supervisors and simulated clients and other stakeholders (e.g. employers) about the quality of the rehabilitation or intervention plan, professional behaviours, communication and self-management
2. High level of complexity requiring student engagement and interaction	
3. Delivered with immediacy to interaction with a real client (may be portrayed by a standardised patient) and to OT clinical placements	• Use of standardised patients/actors and practicing health professionals to enable students to interact with ‘real’ clients and professionals in the simulated practice setting • Supervision of students by practising occupational therapists in the field and tutors with professional practice skills relevant to the SCP
4. Designed and assessed to meet OT clinical placement objectives	• Specific placement objectives and learning outcomes are pertinent to the achievement of foundational clinical practice skills • The learning focus of this SCP is for students to develop core professional practice behaviours and skills. These core professional behaviours and skills are pertinent to all clinical practice areas and include *(1) professional behaviour, (2) self-management skills, (3) co-worker communication and (4) communication skills*
5. No one simulation modality can be used as a ‘stand-alone’ alternative to clinical training time	• Opportunity for students to learn through observation, role modelling and by working alongside each other whilst engaging with a variety of simulation modalities. Modalities will include use of written and video case material, standardised clients, actors and mock (role play) clinical case conferences

The structure and activities of the SCP are based on the Canadian Model of Occupational Performance and Engagement and the Canadian Practice Process Framework [35] to enhance applicability and transferability to various occupational therapy programs. The model and framework are used both nationally and internationally by occupational therapy degree programs to guide occupational therapy students’ clinical reasoning and to enable them to focus on person-centred, occupationally based professional practice. For this trial, materials have been developed to support the SCP, targeting three types of units of study within occupational therapy degree programs: vocational rehabilitation, adult mental health and adult physical rehabilitation. Each of these three *streams* of occupational therapy practice will be part of the trial, with each site able to choose the *stream* that best suits their occupational therapy program. This feature will serve to increase generalisability of the results.

A range of detailed case scenarios have been developed for the three settings, including realistic and comprehensive case file notes and briefing documents that describe clients who require occupational therapy services within one of the three targeted settings. Steps were taken to optimise immersion in the SCP as part of the design process. For instance, university rooms and other spaces used for SCP will be branded with a fictitious placement provider name. A mock corporate placement intranet website with no university branding has been established to host resources and information for students and the staff involved. Client-related forms and referral documents were designed to emulate what might be used by occupational therapy providers and were branded with a logo. To add to the authenticity of the SCP placement, external occupational therapy professionals practising in the relevant field will be employed to provide supervision of the SCP students and to assess students’ learning outcomes.

Implementation of the 40-hour SCP intervention is structured as follows:Students will work with practising clinical supervisors and simulation facilitators in small groups with an SCP supervisor-to-student ratio of 1 to 9 or 10.Tutorial rooms and small offices on the university campus, or off campus if such facilities are available, are allocated for the placement as working spaces for each of the simulated placement days.An induction program is provided on the first day to introduce students to the workplace, supervisor(s), placement structure and content, work processes and expected professional behaviours.Each student will work with two case scenarios in particular, one in significant depth involving a simulation patient, and they will also be exposed to a further two or more cases during the 40-hour SCPStudents will work in small groups (with an average of three students per group, ranging from two to four students) to complete a series of simulation activities pertaining to their primary case scenario involving:
Interactions with a standardised client (simulated patient/actor) to conduct an interview and conduct an activity analysis based on observation of relevant task performance (e.g. preparing lunch or engaging in a workplace task)Engagement with a health professional (e.g. a general practitioner or a social worker) and other relevant stakeholders (e.g. a family member) in the client’s life by telephoneAn assessment of an appropriate external environment such as a workplace, shopping centre or home.
The processes of clinical practice will include initial assessment, interviewing relevant stakeholders, intervention planning, case conferences and documentation. The simulation is designed to replicate real-time, complex and sequential activities as they occur in actual professional practice. Students will work in larger groups for some learning activities.Students will be provided with written documentation such as a client referral, shown a video of a client interview conducted by a professional occupational therapist and provided with a realistic case file document for a simulated client on which to base their own documentation. Students gather clinical information related to a primary client (the simulation patient/client they interview and observe), write up assessment findings, keep daily progress notes and develop an intervention plan for the client.In addition to their active involvement with a simulation client, students will be exposed to further (secondary) cases by responding to a referral of a second client and attending simulated case conferences and case presentations led by other students.Students receive feedback from simulated clients, health professionals, clinical supervisors and teaching staff as the SCP progresses.SCP students incorporate all of the information gathered through the week to prepare a comprehensive file on their client and present intervention recommendations at a case conference held on the final day.

Standardisation of the intervention is supported by a set of resources, explanatory notes, activity guides and other materials, which are incorporated into a set of delivery manuals distributed to each of the eight participating sites. During the development phase, occupational therapy staff members from each partner university, and representing each of the three clinical practice areas (vocational, mental health, physical rehabilitation), contributed to the curriculum through a committee structure to ensure relevance, applicability and authenticity of the materials developed. The manuals are to be adhered to at each site to maximise consistency of SCP delivery. A training officer will provide comprehensive briefings to academics and supervisors at each trial site prior to implementation. This information will also be used to brief professional actors to take on the roles of standardised/simulated clients.

### The TCP comparison group

The TCP will match the SCP in terms of duration (40 hours over 5 days), timing (implemented at the same time or within 1 week of each other), evaluation and setting (vocational rehabilitation, mental health or community-based physical rehabilitation). Students will be placed as individuals or in pairs, according to the needs and limitations of the particular external placement provider.

The learning outcomes for the clinical placement program are the same for the SCP and TCP students and will be communicated to them and the clinical educators prior to placement. The overarching learning outcomes are that students will develop and demonstrate behaviours appropriate to the occupational therapy profession, including:Professional self-conductSelf-management skills (i.e. effective time management, assuming responsibility for own learning, demonstrating initiative and taking responsibility for own actions and responses to supervision and constructive feedback)Effective communication with co-workers and service users and ability to work as part of a teamSkills in effective client information gathering from a range of sourcesAbility to identify a client’s occupational performance issues and assess the impact of environmental and social factors on the client’s ongoing participation and engagement

A comparison of the SCP and TCP pathways is presented in Fig. 3.

**Fig. 3 Fig3:**
[figure not shown]
Comparison between the SCP and TCP intervention pathways

### Instruments and measures

Outcomes will be assessed using a variety of tools to gather both qualitative and quantitative data to address the research questions. Data will be collected immediately prior to or at the beginning of placement, on completion of placement and at the end of the unit of study (see Table 2). Demographic data including student age, gender, university, prior qualifications and prior placement experience will also be collected.

**Table 2 Tab2:** Description of the instruments used to collect data across the trial

Instrument	Type	Timing	Respondent
SPEF-R	Paper-based	Complete across placement week, finalising during morning of 5^th^ day of placement	Clinical supervisors
SPEF-R, self assessment	Paper-based	Complete across placement week, finalising during the 5^th^ day of placement	Students (self-report)
Pre-placement questionnaire	Paper-based	Pre-placement briefing 1 week prior to placement *Or* morning of 1^st^ day of placement	Students (self-report)
Post-placement questionnaire	Paper-based	Afternoon of 5^th^ day of placement	Students (self-report)
SPEF-R, student review	Paper-based	Complete across placement week, finalising during the afternoon of 5^th^ day of placement	Students
Examination	Paper-based	Within 4 weeks of placement conclusion	Students
Sessions evaluation	Online	Within 2 weeks of placement conclusion	SCP students only
Focus group feedback	Transcribed audio	Within 4 weeks of placement conclusion	Students Clinical educators
Clinical educator survey	Online	Within 2 weeks of placement conclusion	Clinical educators (clinical supervisors and simulation facilitators)
Cost data collection	Digital	Across the full extent of the trial	Partner university site coordinators, investigators, placement support staff and project support staff

*SPEF-R* Student Practice Evaluation Form-Revised

#### Written examination (primary outcome)

Whether students who attend the SCP achieve non-inferior outcomes to those attending a TCP in development of professional skills will be determined according to the results of an end-of-placement examination. The written examination will be implemented 1–4 weeks after placement is completed. It will require students to use (1) reasoning skills to integrate knowledge and professional skills relevant to the broad context of the theoretical unit and placement experience (i.e. vocational rehabilitation, mental health or community rehabilitation) and (2) expected professional competencies commensurate to the students’ stage of professional development. The examination will constitute a series of questions based on a scenario-based clinical report provided at the beginning of test. The aim is to test students’ skills in gathering and integrating pertinent information about the client; their capacity to identify relevant occupational performance issues and capacities and environmental barriers to performance; and their skills in identifying further information, sources and methods that could be used to gather information relevant to the client in the scenario.

The examination will be scored using a continuous scale, ranging from 0 to 100%. The examinations will be graded by a panel of clinical educators who will be blinded to the placement type undertaken by each student. They cannot be reliably blinded to university of origin because of the distributed timing of implementation. The panel will use an examination-specific marking rubric [36] and be trained through a series of workshop sessions involving grading a number of examinations and comparing and discussing the relative results. An inter-rater reliability assessment will be employed to track the readiness of each member of the panel to grade student examinations. An ICC of at least 0.7 will indicate acceptable reliability.

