### Blinding

This is a single-blinded RCT where the assessors of the examinations are blind to the group to which students were allocated. Completed examination papers will be checked centrally to ensure no notes are included on the papers that reveal student allocation to SCP or TCP; the papers will then be distributed to markers who have no other role in the study. The examination scores will be collated and entered into the database by the project manager, who is not blinded to student group but has no interaction or history with any of the participating students. The SCP and TCP supervisors and SCP content deliverers cannot be blinded to group, nor can the student participants.

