#### Statistical analyses methods

All data will be entered into a purpose-designed REDCap (https://projectredcap.org/) database, cleaned and assessed for missing data. Summary statistics will be used to describe the sample. To evaluate whether students who attend an SCP achieve non-inferior outcomes to those who attend a TCP, differences in achievement on the post-placement examination score will be evaluated using analysis of covariance (ANCOVA). A mean difference of ≥7 points on the examination score between students will be considered an educationally meaningful difference. Covariates included in the analyses will include broad placement type (vocational rehabilitation, physical rehabilitation or mental health) and any demographic variables identified as important during baseline analyses. Secondary outcomes related to whether students who attend an SCP achieve non-inferior outcomes to those who attend a TCP will be assessed using odds ratios between groups in predicting overall pass/fail grades on the SPEF-R, evaluated using binary logistic regression. Independent variables included in the analyses as possible covariates will include gender, age, broad placement type and any demographic variables identified in baseline analyses as important. Differences between SCP and TCP groups in achievement of a pass/fail grade on each of the four completed sections of the SPEF-R will be assessed using chi-square tests. Scores between SCP and TCP groups for individual SPEF-R items (scored on a 5-point ordinal scale) will be compared using a Mann-Whitney *U* test. An overall difference >1 point on the 5-point scale between groups will be considered educationally important.

To evaluate whether students and clinical educators report similar professional practice learning opportunities during SCP compared to TCP, the differences in frequencies of *not applicable* and *insufficient observation* items checked in the total SPEF-R by (1) students and (2) clinical educators will be compared using an independent samples *t* test, using 95% confidence intervals of the estimated mean difference between groups to identify differences.

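### Marker is not among the listed covariates of the primary ANCOVA, so avoidable between-marker variance can stay in the residual: a modest loss of precision, not a bias

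*Protocol article*

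**What the plan says.** Three sections of the protocol article bear on this.

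- **Written examination (primary outcome).** "The examinations will be graded by a panel of clinical educators who will be blinded to the placement type undertaken by each student". Markers use an examination-specific rubric and are to "be trained through a series of workshop sessions involving grading a number of examinations and comparing and discussing the relative results". Then: "An inter-rater reliability assessment will be employed to track the readiness of each member of the panel to grade student examinations". The numeric standard is "An ICC of at least 0.7 will indicate acceptable reliability". Markers may recognise the university: "They cannot be reliably blinded to university of origin because of the distributed timing of implementation".
- **Blinding.** Papers are checked centrally for notes that would reveal allocation, and "the papers will then be distributed to markers who have no other role in the study". The section gives no rule on how the two arms are spread over markers.
- **Statistical analyses methods.** The primary comparison is an ANCOVA on the examination score. "Covariates included in the analyses will include broad placement type (vocational rehabilitation, physical rehabilitation or mental health"), plus demographic variables found important in the baseline analyses. Marker is not listed. It is neither demographic nor a baseline characteristic, so the second clause does not bring it in.

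The Randomisation and allocation section adds that students are allocated 1:1 in blocks within each site.

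**The concern.** The non-inferiority decision is made in absolute examination points, but the readiness standard for markers is relative. An ICC of 0.7 says that about 70% of score variance lies between students. How many points the other 30% represents depends on how widely the scores spread. If the ICC is of the consistency type, constant severity differences between markers do not enter it at all. Markers can therefore qualify while one is several points harsher than another.

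Such differences are a recordable source of variance. If marker is in the model they are removed. If it is not, they stay in the residual and widen the confidence interval for the difference between simulated and traditional placement. What is at stake is power, in a trial planned at only 0.8 with 20% attrition expected.

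**Working it through.** **Inputs from the Sample size section.** Margin 7 points, power 0.8, alpha 0.05 (sidedness not stated), 120 per group, site ICC 0.007, cluster size 50–60, attrition 20%. No SD is given.

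**1. The plan's own figures.**
- Design effect at cluster size 60: 1 + 59 × 0.007 = 1.413, and 240 × 1.413 = 339, which matches the stated 340. Sizes of 55 and 50 give 331 and 322.
- Attrition: 340 / 0.8 = 425, as stated.
- The 120 per group cannot be checked forwards without an SD. Solved backwards with one-sided 0.025 and true difference 0: SD = 7 × √60 / (1.960 + 0.842) = 19.35. With one-sided 0.05 the implied SD is 21.81. I use 19.35 below, as an assumption.

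**2. What an ICC of 0.7 leaves open.** At the floor, under absolute agreement, the non-student share is 0.30 × 19.35² = 112.3 points squared.
- Two markers a distance g apart contribute g²/2 to rater variance. For g = 7 this is 24.5, which fits within the 30% share for any SD above √(24.5 / 0.30) = 9.0.
- The largest gap that fits is √(2 × 112.3) = 15.0 points at SD 19.35, 10.8 at SD 14 and 7.7 at SD 10. Severity gaps of several points are thus not excluded over this range.

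**3. What it costs the arm comparison.** When two markers share the papers evenly, a gap g adds g²/4 to score variance. For g = 7 this is 12.25, or 12.25 / 374.4 = 3.3% of the total.
- SE with 170 per group (340 evaluable): 19.35 × √(2/170) = 2.10.
- Chance imbalance from a 7-point gap moves the arm difference by an SD of 3.5 × √(2/170) = 0.38 points. This is already contained in the 2.10.

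**4. Gain from adding marker.** Let f be the share of score variance due to severity. The residual SD becomes 19.35 × √(1 − f), and power at 120 per group is Φ(7 / (SD × √(2/120)) − 1.96).

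| Severity assumption | f | Power without → with marker | n per group for 0.80 | SE at 170 per group |
|---|---|---|---|---|
| Two markers 7 points apart | 0.033 | 0.80 → 0.813 | 120 → 117 | 2.10 → 2.06 |
| Half of the 30% is severity | 0.15 | 0.80 → 0.86 | 120 → 102 | 2.10 → 1.93 |
| All of the 30% is severity (upper bound) | 0.30 | 0.80 → 0.918 | 120 → 84 | 2.10 → 1.76 |

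**5. Bias and type I error.** A simulation used 240 students, 2, 4 or 6 markers, papers handed out at random, marker severity SD 4.95 or 10.6, and 4,000 runs per setting. Estimates were unbiased. One-sided type I error at the margin was 0.0235–0.026 without marker and 0.0225–0.028 with it, against a nominal 0.025 (simulation error √(0.025 × 0.975 / 4000) = 0.0025). At severity SD 10.6, power was 0.816–0.860 without marker and 0.904–0.917 with it. At 4.95 it was 0.801–0.811 and 0.808–0.822, a gain hardly larger than simulation error.

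**The case against.** The strongest reply is that much of this is silence in a condensed article. How papers are dealt, and which form of ICC is used, may stand in a marking manual or analysis plan that is not shown. The covariate sentence is also not worded as an exhaustive list. This stands in part: the ICC form is a reporting detail, and a missing dealing rule is no error in itself. What remains is that the article does set out the primary model, and the covariates it names leave marker out.

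Three stronger readings are tempting, and the documents do not support them.

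- *A reader might infer that markers are unbalanced across arms*, perhaps because the two placements may run up to a week apart. The article does not say that papers are batched by arm. Arm-blind marking and 1:1 allocation within site balance markers in expectation, even if markers work site by site.
- *A reader might infer that the ICC is the only control on marking.* The rubric, the calibration workshops, the blinding and the central check of papers are controls too, and the workshops bear directly on severity.
- *A reader might set a gap between two markers beside the 7-point margin between arms.* These are different quantities: a 7-point marker gap moves the arm difference by an SD of only 0.38 points.

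It is also fair to say that added noise makes non-inferiority harder to show, so it does not favour a false claim. If the pilot scores behind the planning already carried marker variation, planned power does not fall short, and adjustment is a gain on top. The article does not say whether they did.

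**Conclusion.** The point holds as a low-severity matter of precision. Marker severity is a recordable component of the primary outcome, the readiness standard does not keep it small in points, and the listed covariates do not remove it. The validity of the comparison is not in question.

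The size is modest and uncertain. The larger gains need severity to take up half or more of a non-student share set at its maximum. The upper bound would mean that markers make no random error at all. The percentage saving in sample size for a given f (15% or 30%) does not depend on the SD, but the share due to a fixed 7-point gap does: 2.6% at SD 21.8, 3.3% at 19.35 and 6.2% at 14. A panel that is well calibrated by the workshops would gain little.

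**What to change.** 1. Deal each site's papers so that every marker receives both arms in equal numbers. The central check already handles every paper, so a person or list outside the marking panel can do this without unblinding markers.
2. Record a marker code with each examination score.
3. Add marker as a factor to the primary ANCOVA. Balanced dealing alone is not enough: unless marker is in the model, its variance stays in the residual and the standard error takes no credit for the balance.

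The Trial status section reports data collection complete at acceptance, so marking may be finished. In that case step 3 is still open wherever a marker code was kept, either as an adjustment or as a sensitivity analysis, specified before the arms are compared.

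The cost is one data column, a sorting rule and a few degrees of freedom. No second marking is needed.
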